## Abstract

Background: The home and family environment is a highly influential psychosocial antecedent of pediatric obesity. Implementation of conventional family- and home-based childhood obesity interventions is challenging for parents, often requiring them to attend multiple educational sessions. Attrition rates for traditional interventions are frequently high due to competing demands for parents’ time. Under such constraints, an Internet-based intervention has the potential to modify determinants of childhood obesity while making judicious use of parents’ time. Theory-based interventions offer many advantages over atheoretical interventions, including reduced intervention dosage, increased likelihood of behavioral change, and efficient resource allocation. Social cognitive theory (SCT) is a robust theoretical framework for addressing childhood obesity. SCT is a behavior change model rooted in reciprocal determinism, a causal paradigm that states that human functioning is the product of a dynamic interplay of behavioral, personal, and environmental factors.
Objectives: To evaluate the efficacy of the Enabling Mothers to Prevent Childhood Obesity Through Web-Based Education and Reciprocal Determinism (EMPOWER) program, an Internet-based, theory-driven intervention for preventing childhood overweight and obesity. The project goal is supported by two specific aims: (1) modification of four obesogenic protective factors related to childhood obesity (minutes engaged in physical activity, servings of fruits and vegetables consumed, servings of sugar-sweetened and sugar-free beverages consumed, and minutes engaged in screen time), and (2) reification of five maternal-mediated constructs of SCT (environment, expectations, emotional coping, self-control, and self-efficacy).
Methods: We will recruit mothers with children ages 4 to 6 years from childcare centers and randomly assign them to either the theory-based (experimental) or knowledge-based (control) arm of the trial. Data for the intervention will be collected at three intervals: baseline (week 0), posttest (week 4), and follow-up (8 weeks). At each phase of data collection, we will collect from both groups (1) measures of the four obesogenic protective factors, and (2) summated SCT construct scores. Constructs will be measured by a psychometrically valid and reliable SCT-based instrument. Behaviors will be evaluated by a behavior log. We will use a repeated-measures one-between-, one-within-participants design to evaluate intervention results. Constructs will be modified through Web-based learning modules, online interactive worksheets, and mother–child home-based activities. Process evaluation will assess program fidelity.

## Introduction

Since 1980 the prevalence of childhood obesity has tripled among school-age children and adolescents in the United States [1]. Etiologically, pediatric obesity is strongly influenced by the environment [2]. Researchers have attempted to modify antecedents of childhood obesity in a variety of environmental contexts, including communities, schools, and after-school programs [3]. From an ecological perspective, the home and family environment is perhaps the most influential psychosocial milieu of pediatric obesity. Parents play an integral role in shaping the eating and exercise behaviors of developing children [4]. Furthermore, children consume an estimated two-thirds of their dietary intake within the home environment [5]. As a result, there has been an increased call for interventions that target young children within the context of the home and family environment [6,7].

However, unlike alternative intervention formats that focus on children as the salient agents of change, researchers implementing family- and home-based interventions have discovered that targeting parents exclusively produces more significant outcomes [8-16]. Within the family and home context, there has been a greater focus on targeting mothers as the primary change agents. It has been well established that overweight and obesity disproportionally affect low-income and minority children. Subsequently, there has been a natural proclivity to integrate family- and home-based obesity programming with maternal-based, government-funded nutrition programs such as the Special Supplemental Nutrition Program for Women, Infants, and Children [17]. Additionally, there is evidence that maternal behaviors including gestational weight gain and smoking contribute to higher risk of pediatric obesity [18]. Breastfeeding has also been cited as a protective factor against childhood obesity [19].

While there is little dispute that parents are powerful change agents in the lives of young children, focusing solely on parents presents several challenges. These barriers must be addressed if family- and home-based interventions are to be accepted as an effective preventative treatment for childhood overweight and obesity. The Enabling Mothers to Prevent Childhood Obesity Through Web-Based Education and Reciprocal Determinism (EMPOWER) program will address four salient barriers confronting the advancement of family- and home-based childhood overweight and obesity interventions: (1) efficacy of theory-based family- and home-based interventions, (2) deficit in theoretical construct measurement, (3) low program participation and high attrition rates, and (4) absence of intervention implementation process evaluation.

### Efficacy of Theory-Based Interventions

We systematically reviewed randomized control trial family- and home-based interventions targeting children ages 2 to 7 years and found that only 3 of the 9 interventions applied a theoretical framework [20]. It is generally recognized that theory-based interventions are more efficacious than atheoretical interventions [21]. The economic advantages of theory-based interventions are primarily attributed to design and measurement efficiencies. Measurement tools for theory-based interventions are developed through psychometric modeling. Validated theoretical models can provide detailed insight into the dynamics that underlie behavior change. By reifying the specific theoretical constructs that predict a given behavior, interventionists can design programs that are more likely to result in behavior modification. To evaluate the efficacy of theory-based family- and home-based interventions, our project will compare the social cognitive theory (SCT)-based EMPOWER intervention (experimental) with an equivalent atheoretical, knowledge-based intervention (control).

### Deficit in Theoretical Construct Measurement

Although theory-based interventions can produce significant outcome measures, it is critical that interventionists operationalize the theories they employ. Concurrently, researchers must measure changes in the reified constructs from before to after the intervention using psychometrically valid instruments. In doing so, they can evaluate theoretical constructs and advance more effective intervention designs. Without adequate measurement, it becomes difficult to determine which mediating variables were attributed to the positive health outcomes of the intervention. Among the family- and home-based theory-based interventions, we were unable to confirm any that operationalized or measured the constructs of the theoretical frameworks the researchers applied. The current investigation will overcome this deficit by operationalizing and measuring five constructs of SCT.

### Low Program Participation and High Attrition Rates

An additional barrier to family- and home-based interventions is the time commitment required of parents to participate in face-to-face educational sessions. Researchers employing family- and home-based interventions have commented that programs emphasizing these modalities have resulted in lower recruitment and retention rates [22]. To maximize participation and retention, our study will employ Web-based learning as the primary catalyst of behavior modification. Online learning offers flexibility and convenience to parents. It also promotes self-paced learning and skill mastery. An Internet-based, theory-driven family- and home-based intervention offers the potential to improve outcome measures, minimize overhead costs, foster program replication, and enable wide-scale intervention dissemination.

### Absence of Process Evaluation of Intervention Implementation

Process evaluation is applied in interventions to evaluate program fidelity, dose, reach, stakeholder satisfaction, and exposure of the intervention modalities. Only two of the family- and home-based interventions we reviewed incorporated process evaluation [10,13]. Among these cases, we were unable to verify any that incorporated intervention implementation process evaluation. Implementation process evaluation is a specific type of process evaluation that examines fidelity of program delivery. Assessment of implementation allows the researchers to ensure the program was delivered to the participants in the prescribed fashion. Failure to evaluate program fidelity can make it difficult to confirm whether nonsignificant program outcomes were due to ineffective intervention components or inadequate transference of intervention deliverables. Our protocol will employ several layers of intervention implementation process evaluation to properly assess outcome measures.

### Specific Aims

#### Specific Aim 1

The American Medical Association, in collaboration with 15 health care organizations, developed a series of recommendations for the prevention and treatment of child and adolescent obesity [23]. The key lifestyle behaviors identified by the committee will serve as the basis for the behavioral outcome measures of this study. The four obesogenic protective factors measured in the intervention will be the child’s (1) engagement in 60 minutes of moderate to vigorously intense physical activity each day, (2) consumption of 3 or more cups of fruits and vegetables each day, (3) replacement of sugar-sweetened beverages with sugar-free beverages, and (4) limitation of screen time (television/computer time) to no more than 2 hours per day.

Therefore, the first specific aim of this study is to compare the effects of the EMPOWER intervention (experimental) with an equivalent knowledge-based intervention (control) on the four identified obesogenic protective factors from baseline (week 0) to postintervention (week 4) and 1-month follow-up (week 8) in children ages 4 to 6 years as measured through a valid and reliable behavior log.

#### Specific Aim 2

SCT is a robust theoretical framework for eliciting behavior change [24]. SCT is based on the premise of reciprocal determinism, a causal model that posits that human functioning is the result of environmental, personal, and behavioral factors. SCT is rooted in human potential and emphasizes modeling, symbolizing, forethought, self-regulatory, and self-efficacy capabilities. The key constructs of SCT will serve as the theoretical outcome measures for the study. The five SCT constructs that will be operationalized for the EMPOWER program will be (1) environment, which comprises the external stimuli to which an individual is exposed, (2) expectations, which are the anticipations that an individual has about a specific outcome and the values the individual places on those outcomes, (3) emotional coping, which is an individual’s ability to control emotional and psychological states associated with acquisition of a new behavior, (4) self-control, which results from explicit and specific goal setting for accomplishing a behavior, and (5) self-efficacy, which results from confidence in personal capability to perform a behavior. 

The second specific aim of this study is to compare the effects of the EMPOWER intervention (experimental) with a knowledge-based intervention (control) on the five SCT maternal-mediated constructs from baseline (week 0) to postintervention (week 4) and 1-month follow-up (week 8) in mothers of children ages 4 to 6 years as measured by a SCT-based instrument.

## Methods

### Instrumentation

In support of specific aims 1 and 2, we are collecting data to develop an instrument capable of measuring the five listed maternal-mediated SCT constructs for predicting the four obesogenic protective factors outlined in this study. Instrumentation will encompass three stages of data collection and analysis. Stage 1 is complete and included evaluation of face and content validity of the instrument by a panel of six experts over two rounds, in addition to readability assessment by the Flesch Reading Ease Test and Flesch-Kincaid Grade Level Test [25]. The instrument was word processed in Microsoft Word Professional 2010 (Microsoft Corporation, Redmond, WA, USA) and analyzed by the software’s readability statistics function. Based on the findings of the software, the instrument had a Flesch Reading Ease Test score of 72%. Scores ranging from 70% to 79% are categorized as “fairly easy” in terms of reading ease [25]. The software populated a Flesch-Kincaid Grade Level test score of 5.7, indicating the reading level of the instrument was between a fifth- and sixth-grade school reading level according to US educational standards [26].

Stage 2 will assess the test–retest reliability of the instrument by having the same group of participants (n = 30) complete the instrument two separate times with 4 weeks between administrations. We have set acceptable test–retest coefficient values a priori at 0.70. Stage 3 will evaluate construct and predictive validity of the instrument through structural equation modeling. Each of the four behavioral determinants of childhood obesity (endogenous variables) will be modeled separately according to the five SCT constructs (exogenous variables). Applying a participant to parameter ratio of 5:1, we will require a sample size of 165 to build each model. The final specified models will serve as the theoretical framework for designing and measuring the EMPOWER intervention.

### Interventions

The most innovative component of the intervention is the novel medium of delivery (see Figure 1). Despite the highly promising potential of Web-based programs, this modality has not been adequately tested and reported in the childhood obesity intervention literature. The proposed brief intervention will span 2 months. The four obesogenic protective factors will be targeted through weekly online modules for a total of four modules. The Internet-based program will be hosted on the University of Cincinnati’s Blackboard Version 9 (Blackboard Inc, Washington, DC, USA) platform. Each week participants will be sent email messages to promote program involvement and participation.

**Figure 1 figure1:**
[figure not shown]
Logic model for the Enabling Mothers to Prevent Childhood Obesity Through Web-Based Education and Reciprocal Determinism (EMPOWER) intervention. SCT = social cognitive theory.

#### Theory-Based Intervention (Experimental)

Each of the four modules for the experimental group will incorporate affective, cognitive, and experiential pedagogical approaches to promote maternal-mediated behavior change in children based on the five selected SCT constructs. Module curricula will include 15-minute audiovisual sessions developed and produced by the research team. Interactive online worksheets and newsletters will complement each module. The interactive worksheets will be designed to reinforce the concepts conveyed in the audiovisual sessions. Self-efficacy for the four obesogenic protective factors will be built through home-based activities completed by participating mothers and their children.

#### Knowledge-Based Intervention (Control)

The complementary and equivalent knowledge-based program will also target the four obesogenic protective factors; however, the control program will not focus on modification of SCT constructs. Instead, the program will center on delivery of general health knowledge regarding the four obesogenic protective factors as opposed to theory-based behavior modification. Newsletters and audiovisual sessions will complement each module, but we will not include interactive components designed to increase self-efficacy in the mothers.

### Intervention Design and Sampling

#### Design

The proposed 8-week program will use a group randomized experimental design to test the efficacy of the protocol. Statistically, we will use a repeated-measures one-between-, one-within-participants design. The protocol will be delivered to two cohorts randomly assigned to receive either the theory-based (experimental) or knowledge-based (control) protocol (see Figure 2). The primary independent variable in the proposed study is the intervention. This is a fixed, categorical variable with two levels: EMPOWER intervention and knowledge-based intervention. The second independent variable in the study is time (within-participants effect). This is also a fixed, categorical variable with three levels: (1) baseline, (2) postintervention (at 4 weeks), and (3) 1-month follow-up (8 weeks after baseline). The outcome measures for comparison between the experimental and control groups are the four obesogenic protective factors and the five SCT constructs.

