#### Sample Size for Efficacy Trial

Based on previous studies, significance criteria for this investigation were set at an alpha of .05, a power at 80%, and an effect size at 0.20 [12,14,27]. We established the number of groups at 2 and the number of measurements at 3. Correlation between repeated measures was set at .05 and nonsphericity correction at 1. Inputting these criteria into G*Power resulted in a sample size of 42 [28]. To account for potential attrition, we inflated the sample size by 20%, resulting in a total sample size of 50 with 25 participants allocated to each group.

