### Data Analysis

We will collect data for the intervention over three phases: phase 1 at baseline (week 0), phase 2 at posttest (week 4), and phase 3 at follow-up (week 8). At each phase of data collection, we will collect from both groups (1) measures of the four obesogenic protective factors, and (2) summated scores for the SCT constructs. SAS version 9.3 (SAS Institute, Cary, NC, USA) will be used to conduct statistical analyses of the intervention. Each of the outcome measures will be tested using PROC MIXED to analyze the data collected in the repeated-measures statistical design. The model will account for gender (male, female) as a potential covariate.

The null hypothesis for the time effect is that the means of the outcome measures at each of the three levels will be equal. If we find statistically significant differences, we will plot least square means and apply the Scheffé post hoc test. Normality of the distribution of outcome measures, homogeneity of variances, and the Mauchly test of sphericity will be used to test the assumptions of repeated-measures analysis of variance. Variables that are not normally distributed or that display variance heterogeneity will be transformed to obtain distributions that are closer to normality and variance homogeneity. The Huynh and Feldt adjustment to any *F*-distribution degrees of freedom will be applied if the covariances between the repeated measures being analyzed do not follow a spherical distribution.

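### Leaving baseline means free in a three-level time factor, with gender the only covariate, gives up precision that baseline adjustment would recover at no cost

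*Protocol article*

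**What the plan says.** The Design section describes one between-participant factor (intervention) and one within-participant factor (time). Of time it says: "This is also a fixed, categorical variable with three levels: (1) baseline, (2) postintervention (at 4 weeks), and (3) 1-month follow-up". Sample Size for Efficacy Trial counts baseline in the same way: "We established the number of groups at 2 and the number of measurements at 3".

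Data Analysis fits this design in PROC MIXED for each outcome. On covariates it says only: "The model will account for gender (male, female) as a potential covariate". It words its null hypothesis as equality of the means over all three time levels, and adds the Mauchly test and the Huynh-Feldt adjustment, which belong to classical repeated-measures analysis of variance. Nowhere is the baseline value a covariate, and nowhere are the two arms' baseline means set equal.

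**The concern.** In a two-arm, three-occasion model with free means, the treatment effect is the group-by-time interaction: change from baseline in one arm minus change in the other. That contrast subtracts a noisy baseline measurement in full. Participants are randomised, so the true baseline means do not differ between arms, and a model that uses this fact estimates the same effect with a smaller standard error.

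The trial enrols 50 and was sized on 42. Its Limitations section warns that the timeline may be too short to show behavioural change, and that behaviours rest on 24-hour recall that may not reflect a typical day. Precision is scarce here, and every outcome is already measured at baseline.

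**Working it through.** **Inputs.** From Sample Size for Efficacy Trial: "significance criteria for this investigation were set at an alpha of .05, a power at 80%, and an effect size at 0.20"; 2 groups and 3 measurements; "Correlation between repeated measures was set at .05 and nonsphericity correction at 1"; "Inputting these criteria into G*Power resulted in a sample size of 42". From Instrumentation: an acceptable 4-week test-retest coefficient of 0.70 for the SCT instrument. Assumptions: effect size 0.20 is Cohen's f; unit SD; equal correlation ρ between all visits; 21 completers per arm.

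**1. The plan's own figure.** For the within-between interaction, λ = f²·N·m/(1−ρ), with df 2 and 2(N−2).
- ρ = .05 as printed, N = 42: λ = 0.04 × 42 × 3/0.95 = 5.31, power 51.3%. For 80% power, N = 78 is needed.
- ρ = .50, N = 42: λ = 0.04 × 42 × 3/0.50 = 10.08, power 80.3%. The required N is exactly 42.

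So .50 reproduces the stated size and .05 does not. The main figures below use .50.

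**2. Variance of the treatment effect** (in units of 2σ²/n):
- One follow-up visit: difference in changes 2(1−ρ); baseline-adjusted 1−ρ².
- Mean of weeks 4 and 8: difference in changes 1.5(1−ρ); baseline-adjusted (1+ρ)/2 − ρ².

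| ρ | One visit: change → adjusted | Saving | Two-visit mean: change → adjusted | Saving |
|---|---|---|---|---|
| .50 | 1.00 → 0.75 | 25% | 0.75 → 0.50 | 33.3% |
| .70 | 0.60 → 0.51 | 15% | 0.45 → 0.36 | 20% |
| .05 (printed) | 1.90 → 0.9975 | 47.5% | 1.425 → 0.5225 | 63.3% |

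A three-visit mixed model with baseline means constrained equal gives the same single-visit variance as covariate adjustment (ratio to the free-means model 0.75 at .50 and 0.525 at .05).

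**3. Effect size in SD units.** Suppose the difference d is absent at baseline and equal at weeks 4 and 8. The interaction noncentrality is then n·d²/(3(1−ρ)). Setting this equal to f²·2n·3/(1−ρ) gives d² = 18f² = 18 × 0.04 = 0.72, so d ≈ 0.85.

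**4. Power of the 2-df test, 21 per arm.** The adjusted noncentrality is n·d²/(1+ρ−2ρ²).
- ρ = .50: 21 × 0.72/1.5 = 10.08 (80%) against 21 × 0.72/1.0 = 15.12 (about 93%).
- ρ = .70: 16.8 (96%) against 21.0 (98%).
- ρ = .05: 5.31 (51%) against 14.47 (92%).

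**5. One visit at ρ = .50.** For an effect that the change contrast detects with 80% power at 42 completers (0.886 SD), the adjusted contrast has 89.8% power, or reaches 80% with 34 completers.

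**The case against.** The strongest defence is that a three-level repeated-measures analysis is conventional and valid. Under randomisation the group-by-time contrast is unbiased, its standard error already includes the baseline noise, and the trial was sized for the same three measurements. All of that stands. A reader might infer that the planned analysis is biased, or that chance baseline imbalance invalidates it. The documents do not support this: what is lost is precision.

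A reader might also infer that having baseline on the outcome side is itself the fault. It is not. A three-level model with equal baseline means is as efficient as covariate adjustment, so the loss comes only from leaving those means free. The article does not spell out the parameterisation, but its classical design and sphericity language make free means the natural reading.

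A third tempting inference is the dramatic one from the printed correlation, 51% power rising to 92%. That correlation does not return the protocol's own N, so it cannot carry the headline. The five SCT constructs, if they meet the 0.70 target, would gain only modestly. That figure is a target and not a result, and no correlation is given for the four behaviours beyond the planning value.

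Finally, model details can be left to an unseen analysis plan. Here, however, the article states a specific model and names its covariate, so the choice is open to comment.

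If the intended test were instead the group main effect over three levels, the loss would be greater. At ρ = .50 the baseline level dilutes a sustained effect to 2d/3 with variance (1+2ρ)/3, giving information (4/9)/(2/3) = 0.67 against 1/0.50 = 2.00.

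**Conclusion.** The point holds as a matter of efficiency. The model as described discards precision that randomisation and the existing baseline data make available. At ρ = .50 the saving forgone is 25% of the variance at one visit and 33% for the two-visit mean. Equivalently, power is about 80% where 93% was attainable with 42 completers. The power figures rest on reading 0.20 as Cohen's f, equal effects at both follow-ups and equal correlations between visits. The loss shrinks to 15% to 20% of the variance at .70. It would reach 47.5% to 63% only if the printed .05 were the true correlation. The plan's inference remains valid either way.

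**What to change.** In PROC MIXED, take weeks 4 and 8 as the repeated outcomes, with group, visit, group-by-visit, the baseline value of the same outcome, baseline-by-visit and child gender. Alternatively, keep all three visits and constrain the baseline means to be equal between arms. Under either model, report the adjusted between-arm difference at each visit.

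The cost is a change of model wording. Baseline is already collected for all nine outcomes, and no extra participants, visits or software are needed.
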